# Study protocol (main points)

# The nutrition-based comprehensive intervention study on childhood obesity in China

Objective

The main purpose of the intervention study is to evaluate the feasibility and effectiveness of the comprehensive intervention program for childhood obesity which combined nutrition education and physical activity interventions. The second purpose of the intervention study is to compare the cost-effectiveness of the comprehensive intervention strategy with two other interventions, one only focuses on nutrition education, the other only focuses on physical activity. The final aim of the study is to raise the awareness of the national childhood obesity prevention and control policy recommendations

Study design

The study will be designed as a multi-centred randomiised controlled trial, which included 6 centres located in Beijing, Shanghai, Chongqing, Shandong province, Heilongjiang province and Guangdong province. Both nutrition education and physical activity intervention will be implied in all intervention schools of 5 cities, while in Beijing, nutrition education intervention will be implied in 3 schools and physical activity intervention among the other 3 schools. Nothing will be done in control schools.

Participants

A total of 9750 primary students (grade 1 to grade 5, aged 7-13 years) will participate in baseline and intervention researches of questionnaire, physical examination, physical quality test and blood biochemistry and so on. The study design in each center is presented in Figure 1. The method of two-step cluster sampling will be adopted. The first step is that randomly selected 6 schools from each centre assigned to either intervention (3 schools) or control condition（3 schools）. The second step is that randomly choose 2 classes from each grade, totally, around 250 subjects will be randomly selected from each school.

Figure 1 Study design in each center

Sample size calculations

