The variable used for the calculation of sample size is the BMI changes. To detect a difference of 0.7 kg/m2 of BMI changes between the intervention and control groups, the minimum number required would be 3 schools in each center with 250 students in each school. The intraclass correlation is assumed to be 0.05. The sample size of 7500 students from 30 schools located in 5 centers has 90% power to detect a mean between-group difference in BMI of 0.7 units with an effect size of 0.64. Statistical significance is set at 5% (two-sided). Another 2250 students from 9 schools are randomly chosen only for cost-effect analysis, 3 schools for nutrition intervention, 3 schools for physical activity intervention and another 3 schools are treated as control schools.

Intervention

Three interventions will be included in present study: nutrition education, physical activity intervention and comprehensive intervention, the detail strategies are shown in Table 1.

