Initially, the descriptive statistics will be calculated for all variables considered. Anthropometric measurements at baseline will be compared between intervention and control groups using multivariate regression analysis with age and sex in the model. The effects of intervention will be analyzed using mixed procedure, with BMI changes from baseline as the primary outcome variable. The fixed effects include baseline BMI, age, sex, and the intervention group. The schools within center will be treated as a random effect variable. Similar mixed models will be constructed for other outcome variables, including weight, height, BMI z score, fat free mass, fat mass, percent body fat, physical fitness, as well as the chronic disease factors including glucose, insulin, TG, TC, HDL, LDL and blood pressure.

The intervention effect on body composition will be compared according to the real diet and physical activity changes while the intervention effect on chronic disease factors will also be compared between students whose BMI z score increased or not.

Both cost-effectiveness and cost-benefit will be economically analyzed to compare the three strategies, including nutrition education intervention, physical activity intervention and the comprehensive intervention.

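### Schools are allocated 3:3 within centre, but the primary model, read literally, gives centre no effect of its own, so the test of the intervention is conservative if centres differ

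*Protocol*

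**What the plan says.** **Allocation.** Under Participants, the Protocol says "randomly selected 6 schools from each centre assigned to either intervention (3 schools) or control condition". Centre is therefore a stratum of the allocation. The sample size section bases the main comparison on 30 schools in five centres, that is, 15 schools per arm. Beijing differs. The nine further schools are described as "3 schools for nutrition intervention, 3 schools for physical activity intervention and another 3 schools are treated as control schools", and they are chosen for the cost-effect analysis only.

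**Primary model.** Under Analysis strategy, intervention effects are to be "analyzed using mixed procedure, with BMI changes from baseline as the primary outcome variable". The terms follow: "The fixed effects include baseline BMI, age, sex, and the intervention group". Next comes "The schools within center will be treated as a random effect variable". The same structure is then extended to weight, height, BMI z score, body composition, fitness, blood measures and blood pressure.

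The list of fixed effects has no centre. Centre appears only as the level within which schools are nested.

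**The concern.** When clusters are allocated in equal numbers within strata, differences between strata cancel from the treatment contrast. The analysis has to take the stratum variance out of the error term for the standard error to reflect this. A random effect for school within centre, on its own, only labels the 30 schools uniquely and gives schools in the same centre nothing in common. If BMI change differs between centres, that variation is counted as variation between schools, and it enters the error for the intervention effect although the design has removed it from the estimate.

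At stake are confidence intervals wider than the design warrants and a test that rejects less often than its nominal level. This applies to the primary outcome and to every outcome analysed with a similar model. Some centre differences are plausible: the centres are in different cities and provinces, and each centre's own staff train its teachers.

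**Working it through.** **Inputs from the Protocol (sample size section).** Difference 0.7 kg/m2; effect size 0.64, so SD = 0.7/0.64 = 1.094; intraclass correlation 0.05; 250 students per school; 15 schools per arm; two-sided 5%.

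**The plan's own power figure.** The Protocol says the 30 schools have power as follows: "has 90% power to detect a mean between-group difference in BMI of 0.7 units with an effect size of 0.64".
- Design effect = 1 + 249 × 0.05 = 13.45.
- Standard error with 15 schools per arm = 1.094 × √(2 × 13.45/3750) = 0.093, so 0.7 is about 7.6 standard errors and power is about 100%, not 90%.
- The 90% is close to the figure for a single centre: 52 students per arm × 13.45 = 699, or 2.8 schools of 250, rounded up to 3. With 3 schools per arm, power is 92% by the normal approximation and 72% with t on 4 degrees of freedom.

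This mismatch is a separate matter. Here it shows only that power for 0.7 kg/m2 is ample in 30 schools.

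**Assumption.** The Protocol does not say whether 0.05 includes between-centre variance, and it gives no split. I take 0.05 as the total and let a share s of it lie between centres.

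**Standard errors, in units of the total variance.**
- Variance of a school mean within a centre: W = 0.05(1 − s) + 0.95/250 = 0.05(1 − s) + 0.0038.
- Centre effects cancel under 3:3 allocation, so the true standard error is 1.094 × √(2W/15).
- Without a centre term, the model uses the spread of the 15 school means within each arm. Five centres with three schools each contribute an expected sum of squares of 3 × 4 = 12 times the centre variance, on 14 degrees of freedom. So 12/14 of the centre variance is added, and the reported standard error is about 1.094 × √(2(W + 0.05s × 12/14)/15).
- For s = 0.5: W = 0.0288 and the added part is 0.0214, so the ratio is √(0.0502/0.0288) = 1.32.

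**Simulation.** 40,000 trials of school means for each share, five centres × two arms × three schools. The model without centre was tested on 28 degrees of freedom (30 − 2) and the model with fixed centre on 24 (28 − 4). The 0.2 kg/m2 is an illustrative smaller effect and is not in the Protocol.

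| Share s | SE with centre | SE without centre | Ratio | Type I error without / with | Power at 0.2 kg/m2 without / with |
|---|---|---|---|---|---|
| 0% | 0.093 | 0.093 | 1.00 | 5% / 5% | 55% / 55% |
| 25% | 0.081 | 0.091 | 1.12 | 3% / 5% | 57% / 66% |
| 50% | 0.068 | 0.090 | 1.32 | 1.5% / 5% | 61% / 81% |
| 75% | 0.051 | 0.088 | 1.72 | 0.6% / 5% | 66% / 96% |

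The figures are rounded. At the planned difference, even the larger standard error of 0.093 leaves 0.7 more than seven standard errors from zero, so power is near 100% in every row under both models.

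The calculation works on school means with equal school sizes and does not model the student-level covariates. If 0.05 instead describes schools within a centre only, the true standard error stays at 0.093 and any centre variance comes on top. The direction is the same.

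**The case against.** **The wording may already include centre.** The random-effect sentence could be shorthand for two nested random effects, one for centre and one for school within centre. Centre would then be in the model and the loss would disappear. This stands as a possible reading. Against it, the sentence names one random variable, and it is schools. Since this section itself lists the terms of the primary model, one that can be read both ways needs a word more, and the fix settles either reading.

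**The loss may be nil.** It depends on between-centre variance in BMI change that remains after adjustment for baseline BMI, age and sex. The Protocol gives no such figure, and with none there is no loss. This also stands, so the percentages above are a range under an assumption and not an estimate for this trial.

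**The planned effect is not at risk.** Power for 0.7 kg/m2 is near 100% with or without centre. This stands. A reader might infer that the primary conclusion is in danger at the planned difference, and the document's own inputs do not support that.

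**Bias.** A reader might infer that leaving centre out biases the result or inflates false positives. It does neither. With 3:3 allocation in every one of the five centres, centre effects cancel from the estimate whether or not they are modelled, and the error in the test is on the conservative side.

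**Beijing.** A reader might also infer that the single-intervention arms in Beijing will be compared with controls pooled over all six centres, which would mix intervention with centre differences. That would follow only if the nine schools entered this model. Analysis strategy does not expressly exclude them, but the sample size section reserves them for the cost-effect analysis and bases the main comparison on the other 30 schools. The documents do not show that pooling is planned.

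**Conclusion.** The point holds as a matter of precision. On the literal reading of Analysis strategy, the primary model leaves out the stratum within which schools were allocated, and any between-centre variance enlarges the standard error of an estimate that is itself unbiased. With a total intraclass correlation of 0.05 and a between-centre share of 0% to 75%, the overstatement runs from nothing to about 72%, and the true type I error from about 5% down to about 0.6%.

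The conclusion rests on three things: school within centre is the only random term, BMI change varies between centres, and allocation is balanced in the five centres. The first is the natural reading but not the only one, and the second is not quantified in the document. What can be gained is narrower intervals and better power for effects below 0.7 kg/m2, and likewise for the other outcomes, for which the Protocol gives no detectable difference.

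**What to change.** In Analysis strategy, write the primary model as BMI change on baseline BMI, age, sex, intervention group and centre (fixed, five levels), with a random intercept for school within centre. State that it is fitted in the 30 schools of the five comprehensive-intervention centres, and use the same structure for the other outcomes.

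Say explicitly that the nine Beijing schools are outside this model, in line with their stated purpose, and that any comparison of the Beijing arms uses the Beijing control schools.

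The cost is one line of text and four of the 28 between-school degrees of freedom. The two-sided 5% critical value moves from 2.05 on 28 degrees of freedom to 2.06 on 24. If centres do not differ at all, power at the illustrative 0.2 kg/m2 falls by about half a percentage point (55.2% to 54.7% in simulation).

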**Table 1 Contents of interventions**

| Group | Interventions |
| --- | --- |
| control group | No intervention |
| Physical activity intervention group | 1. "Happy 10" campaign(2 times/day 10 minutes/time or 1 time/day 20 minutes/time)  2. Parents , health workers / health education teacher: "happy 10" training. |
| Dietary intervention group | 1. Students take part in "Nutrition and Health" classes  2. Parents participate. in "nutrition and health" classes. Give parents corresponding publicity materials.  3. Teacher, health / health education teacher participate in "nutrition and health" classes. Give them corresponding publicity materials.  4.School canteen managers, operators, competent leadership and staff room participate in "nutrition and health" classes.  5. Give them corresponding publicity materials. |
| Comprehensive (Dietary & Physical activity) intervention group | Happy 10+nutrition education  1. Students take part in "Nutrition and Health" classes  2. "Happy 10" campaign(2 times/day 10 minutes/time or 1 time/day 20 minutes/time  3. Parents participate. in "nutrition and health" classes. Give parents corresponding publicity materials.  4. Teacher, health / health education teacher participate in "nutrition and health" classes. Give them corresponding publicity materials. And give them a "happy 10" training.  5. School canteen managers, operators, competent leadership and staff room participate in "nutrition and health" classes. |

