**Outcome measures**

Measurements will be collected in the summers of 2009 (baseline) and in summer 2010 (intervention). Children will be fasted the night before and measured the next morning by trained research staff. Consistent assessment methods will be used throughout the study.

Tables 2 Description of outcomes

| Name of Outcome | Category of Outcome | Description |
| --- | --- | --- |
| Physical examination | Primary outcome | Height, weight, waist circumference, blood pressure |
| Body Composition | Primary outcome | Bioelectrical impedance, single-standard Water Law |
| Blood biochemical indices | Primary outcome | Blood glucose, blood cholesterol, blood triglycerides, blood high-density lipoprotein, low density lipoprotein in blood, blood insulin |
| Dietary intake situations | Primary outcome | 24-hour record of 3 days dietary questionnaire |
| Physical activities | Primary outcome | Seven days of physical activity recall questionnaire, wearing the energy monitoring device, a 24-hour physical activity record sheet |
| Physical measurements | Primary outcome | Standing long jump, 50 m, 50 m × 8 from the run |
| School basic conditions | Secondary outcome | Number of students, the class distribution of the floor, the school's facilities and equipment, sports arrangements, nutrition-related staffing, students in the school dining situation |
| Obesity-related knowledge, attitudes and practices | Primary outcome | Primary school students questionnaire, parents questionnaire, teacher questionnaire, food service personnel questionnaire |
| Cost | Primary outcome | Cost related to intervention material, training, supervisor, teachers time input, transportation, |

Analysis strategy

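### The plan compares intervention effects between groups of children defined by follow-up responses (BMI z change, achieved diet and activity change), so these contrasts are subject to bias and should be reported as associations

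*Protocol*

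**What the plan says.** The last part of the Protocol, Analysis strategy, first sets out mixed models that compare whole arms. The main one has BMI change as outcome and adjusts for baseline BMI, age and sex, with schools within centre as a random effect. It then extends the approach: "Similar mixed models will be constructed for other outcome variables, including weight, height, BMI z score, fat free mass" and further body-composition, fitness and metabolic variables, including glucose, insulin, lipids and blood pressure.

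One further sentence adds two conditional comparisons:

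- For body composition: "The intervention effect on body composition will be compared according to the real diet and physical activity changes".
- For metabolic risk: "the intervention effect on chronic disease factors will also be compared between students whose BMI z score increased or not".

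The sentence names no model for either comparison. It does not call them exploratory or associational, and it names no method, such as mediation analysis or principal stratification, that would support a causal reading.

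**The concern.** Schools are randomised: "randomly selected 6 schools from each centre assigned to either intervention (3 schools) or control condition". That makes whole arms comparable. It does not make subsets of the arms comparable once the subsets are chosen by how children responded.

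A child whose BMI z score rose despite the intervention is likely to differ, in ways that may also affect glucose or lipids, from a control child whose BMI z score rose with no intervention. The same holds for children grouped by the diet or activity change they achieved. The difference between arms within a group then mixes any real effect with a difference in the kind of children compared.

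The Protocol calls the result an intervention effect, lists blood indices, blood pressure and body composition as primary outcomes in Table 2, and aims to inform national policy. A stratum-specific finding could therefore carry causal weight that it has not earned.

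**Working it through.** **Step 1. Are the grouping variables post-randomisation outcomes?**

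- *Timing.* Outcome measures gives one baseline (summer 2009) and one follow-up (summer 2010). Any change or increase needs the 2010 value.
- *BMI z score.* It is listed among the outcomes of the mixed models in Analysis strategy.
- *Diet and activity.* Table 2 has "Dietary intake situations | Primary outcome" and "Physical activities | Primary outcome".
- *Target of the intervention.* Table 1 describes the comprehensive arm as "Happy 10+nutrition education", so it acts directly on diet and activity.

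All three grouping variables are therefore outcomes that the intervention is meant to move.

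**Step 2. How large could the artefact be?** The Protocol states no figure for this comparison, so there is none to reproduce. The illustration covers the BMI z split only.

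Inputs:

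- Shift in BMI z change: 0.64 SD. This is the effect size in Sample size calculations, which is for BMI; using it for BMI z change is an assumption. Smaller shifts of 0.2 and 0.27 SD are also assumed.
- Control mean of BMI z change 0, SD 1, cut at 0: assumed.
- Correlation r between the risk factor and residual BMI z change: assumed, 0 to 0.5.
- True intervention effect on the risk factor: zero, by construction.
- Clustering is ignored.

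Model: Z = −s·T + e and Y = r·e + noise, where T = 1 for intervention and s is the shift. With φ and Φ the standard normal density and distribution function, intervention minus control is:

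- Increased: r × [φ(s)/(1 − Φ(s)) − φ(0)/0.5]
- Not increased: r × [φ(0)/0.5 − φ(s)/Φ(s)]

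At s = 0.64:

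- Increased: r × (1.245 − 0.798) = 0.447r, which is 0.134 SD at r = 0.3.
- Not increased: r × (0.798 − 0.440) = 0.358r, which is 0.107 SD at r = 0.3.

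Under these inputs 50% of control children but only 26% of intervention children fall in the increased group, so the groups no longer hold comparable children.

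| Shift (SD) | r | Increased (SD) | Not increased (SD) |
|---|---|---|---|
| 0.64 | 0 | 0 | 0 |
| 0.64 | 0.3 | 0.13 | 0.11 |
| 0.64 | 0.5 | 0.22 | 0.18 |
| 0.27 | 0.3 | 0.05 | 0.05 |
| 0.2 | 0.3 | 0.04 | 0.04 |

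A simulation of 4,000,000 children, allocated 1:1, gives 0.134 and 0.108 SD for the second row. The undivided arms differ by 0.00, as they should.

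**Step 3. Does the direction hold in general?** Suppose instead that BMI change itself drives the risk factor, Y = r·Z + noise, with r = 0.3 and s = 0.64. The true overall effect is 0.3 × (−0.64) = −0.19 SD. Within groups:

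- Increased: 0.3 × (−0.64 + 0.447) = −0.06 SD.
- Not increased: 0.3 × (−0.64 + 0.358) = −0.08 SD.

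The distance from the overall effect is the same as before (0.13 and 0.11 SD), but it now appears as an understated benefit and not as harm.

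**The case against.** The strongest reply has four parts.

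- *These comparisons are additional.* Analysis strategy already plans whole-arm mixed models for BMI change, body composition and the metabolic factors. No sample size or decision rule rests on the conditional comparisons. This stands, and it limits the point to one sentence of the plan.
- *Bias is not certain.* It needs the intervention to shift the grouping variable, and that variable to share causes with the outcome. The trial's premise supplies the first. The second is plausible for adiposity and metabolic markers, but the documents do not establish it, and at zero correlation there is no bias. This stands, so the right term is subject to bias.
- *The figures are assumed.* The correlation, the cut point and the use of a BMI effect size for BMI z change are not given for this purpose, and no figure is worked for the diet and activity grouping. This stands; the numbers are illustrative only.
- *The sentence could mean a dose-response or mechanism analysis.* That both arms are split is an inference, since no model is named, and a SAP that is not at hand might say more. This stands only in part. The Protocol's own text speaks of comparing an intervention effect between children classified by response, and that wording invites the causal reading whatever model follows.

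A reader might go further and infer that the plan will show false harm, or a benefit confined to responders. Neither follows. Step 3 of the working shows that the apparent direction depends on the assumed mechanism. In the no-effect model both groups err in the same direction and differ from each other by only 0.134 − 0.107 = 0.027 SD, so that model gives no responder-only benefit.

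**Conclusion.** The point holds for this one sentence. Comparing intervention effects across groups defined by BMI z change, or by achieved diet and activity change, conditions on post-randomisation outcomes. The resulting differences between arms are subject to bias and should not be read as intervention effects.

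The documents fix neither size nor sign. Under the stated assumptions the artefact is about 0.11 to 0.13 SD at a 0.64 SD shift and a correlation of 0.3, about 0.04 to 0.05 SD at shifts of 0.2 to 0.27 SD, and nil at zero correlation.

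It would be wrong to infer that the trial's effect estimates in general are compromised. The primary model for BMI change and the matching whole-arm models for the other outcomes do not condition on follow-up responses and are unaffected.

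**What to change.** Reword the sentence in Analysis strategy so that both analyses are reported as observational associations:

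- Regress change in each chronic disease factor on change in BMI z score.
- Regress change in each body-composition measure on change in diet and in physical activity.
- Adjust each model for group, baseline value, age and sex, and keep the random effect for schools within centre that the main model uses.
- State that no coefficient from these models, including the one for group, is an intervention effect.

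If effect modification is wanted, test interactions of group with baseline BMI z score, baseline diet or baseline activity in the same mixed model.

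The cost is a change of wording and some model terms, with no new data. Two things are given up: the change-based analysis no longer supports a causal subgroup claim, and the baseline interactions answer a different question, namely who benefits, and not whether achieved change goes with change in risk. The relabelled regressions keep that second question.
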